#### Manipulation Check

To check if patients in both conditions engaged in mental imagery, they will be asked to note how vivid the imagery was: After each imagery exercise in the ImRs condition, the patient will be asked to note how vivid the imagery of the respective situation was on a scale from 1 (not vivid at all) to 10 (extremely vivid). To check if the session contained any deviations from protocol, the study therapists will be asked to report any deviations from protocol after each session. To ensure that the conditions are executed as intended, all sessions will be recorded on video and evaluated by two independent raters for adherence to the protocol (adherence scales for both interventions were worked out by the study group).

### Experimental Condition: ImRs

The ImRs intervention is based on previous experimental ImRs protocols (Arntz & Weertman, 1999; Ma & Lo, 2022). The relaxation intervention in the control group is based on standardized relaxation protocols (Toussaint et al., 2021).

#### ImRs Session 1 and 2

During ImRs intervention Sessions 1 and 2, participants will be asked to choose one of the three distressing memories. Then they will be asked to delve into the distressing (childhood) memory in their imagination. They will be asked to give a verbal narrative of the contextual and sensory details of the event by questions as for example “what do you see?”, “what do you hear?” and “who else is there?”, as well as to experience and report the emotions that are activated, to share thoughts that go through their mind, and to express what they emotionally need. When the participants’ emotions are sufficiently activated and the most difficult part of the memory is imagined, the therapist will step into the image and change the outcome to a positive ending. The therapist assists the younger self of the participant in addressing the distressing situation, which may include confronting a perpetrator if present. The therapist helps in defending and supporting the younger self of the patient. The therapist will then take care of all other emotional needs of the younger self, helping to process associated emotions and reduce the emotional distress linked to the event. This may involve introducing a sense of safety or control, and when applicable, confronting any responsible parties. Examples of interventions include providing comfort, offering protection, or empowering the younger self. The therapist continues to support the child or younger self of the participant until feeling safe and having all emotional needs satisfied.

#### ImRs Session 3

During ImRs Intervention Session 3, participants will delve into their remaining (childhood) memory in their image and will be again asked to give a verbal narrative of the contextual and sensory details of the event, as well as to share the emotions, thoughts and needs that are activated. At the most difficult moment the patient is instructed to change perspective and imagine to enter the scene as their present adult self and help their younger self. As modelled in the two sessions by the therapist, the adult self should now intervene in the situation. This may involve addressing a perpetrator and taking care of the needs of the younger self. In the final phase, participants will be asked to once again alter their perspective, this time re-entering the scene as their younger self to experience the support and intervention of their adult self. The younger self is also encouraged to request additional interventions as needed.

#### Possible Variations of the Sessions

If the participants want to rescript a distressing memory that was not explored in the introductory session, they will be allowed to use that new situation. In that case, the therapist will briefly assess the new memory using the same structure as in the introductory session (content, age, context, core beliefs, emotional impact), ensuring continuity and consistency of the intervention. If participants do not wish or feel able to personally assist their younger selves in the third session, the session can be conducted as in Sessions 1 and 2.

### Control Condition: Mental Imagery Relaxation Condition

The intervention in the control condition will be an imagery-based relaxation exercise based on established protocols (Toussaint et al., 2021). As in the experimental condition, there will be three experimental sessions lasting between 60 – 90 minutes. Guided imagery relaxation is an established technique for stress reduction. Its effectiveness in reducing symptoms of depression, anxiety, and stress has been demonstrated in several studies (Apóstolo & Kolcaba, 2009; Beizaee et al., 2018; Costa & Barnhofer, 2016). The intervention periods in these studies ranged from one week to four weeks, indicating its potential to produce measurable effects within a relatively short time frame. During this intervention positive imagery is used to invoke sensory experiences and physiological responses. Participants will be given the choice between different topics (e.g. a beach, a forest, a lake, a sky full of stars). Then they will be instructed to sit down in a comfortable manner and to imagine themselves in the scene. The therapist will read out a text about the scenery (e.g. how does the sand under their feet feel). The imagery will be combined with breathing exercises. If time permits participants might complete several relaxation imagery exercises during one session with short intermediate breaks.

### Data Analyses

To address the longitudinal nature of our data and potential missing values, we will employ a multilevel approach. This method allows us to model individual trajectories of change over time while accounting for between-person differences. The multilevel model will include time as a within-subject factor and condition as a between-subject factor. The interaction effect between time and condition is of main interest, as it will indicate whether the rate of change in depressive symptoms differs between the intervention and control group. All primary analyses will be conducted using an intention-to-treat (ITT) approach, including all randomized participants. Missing data will be handled using mixed-effects models, which are robust to missingness under the assumption of missing at random. Analysis will be conducted in R (R Core Team, 2025). In case of substantial differences between conditions in demographic or any of the potentially confounding variables listed previously (e.g., number of CBT sessions before intervention), the variable(s) will be added as covariates to the model. For the analysis of secondary outcomes (e.g., repetitive negative thinking, emotional capabilities, self-compassion, self-esteem), we will employ a similar multilevel modelling approach. Each secondary outcome will be analysed separately, with time and condition as predictors, and the time-by-condition interaction as the primary effect of interest. Given the number of secondary outcomes, we will apply a correction for multiple testing to mitigate the risk of Type I errors across models. Effect sizes will be reported alongside *p*-values to aid interpretation. Results will be treated as exploratory, and full model outputs (including corrected and uncorrected *p*-values) will be provided in the supplementary material to ensure transparency. This will allow us to examine how these outcomes change over the course of the study and whether these changes differ between the ImRs and control conditions.

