### Sample Size

Previous research has demonstrated the effectiveness of Imagery Rescripting (ImRs) in treating various mental disorders, with large effect sizes reported when compared to inactive control conditions (Morina et al., 2017). Ma and Lo (2022) conducted a randomized controlled trial comparing ImRs to cognitive restructuring (CR) in depression treatment. Their findings revealed that both ImRs and CR led to significant reductions in depressive symptoms, with medium to large effect sizes observed. In the present study, we aim to build on these findings by comparing ImRs to an active control condition (relaxation) in the context of ongoing Cognitive Behavioural Therapy (CBT) for depression. Since both study arms receive standard CBT and the control condition is active rather than passive, we expect smaller between-group differences than in previous trials. Specifically, we anticipate moderate differences in the reduction of depressive symptoms between the two interventions. To determine the required sample size, we conducted a simulation-based power analysis using the simr package in R. The analysis was based on a linear mixed-effects model that reflects the longitudinal structure of the study, including four repeated measurement points and a random intercept for each participant. Assuming a moderate group × time interaction effect (β = 0.25) at the final follow-up (FU2), the simulation indicated that a total sample size of approximately 60–70 participants would yield a statistical power of 85–90%. To account for potential dropouts while keeping the study feasible in terms of recruitment and implementation effort, we planned a total sample size of 66 participants with equal allocation to both conditions. This sample size is expected to be sufficient to detect moderate effects over time.

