### Measures

#### Primary Outcome

Changes in Depressive Symptom severity, assessed by the Beck Depression Inventory-II (BDI-II; Beck et al., 1996) will be the primary outcome. The BDI-II is a 21-item self-report instrument assessing depressive symptoms. The items are rated from 0 to 3, with 3 for the most depressed mood. A score 0 – 13 indicates minimal depression, 14 – 19 mild depression, 20 – 28 moderate depression and 29 – 63 severe depression. The BDI-II will be measured before randomization (baseline), one week after the last session (post-intervention) and 4 weeks and 8 weeks after the last session (follow-up). The BDI-II was chosen as the primary outcome due to its strong psychometric properties, sensitivity to change, and feasibility for repeated online assessments, thereby minimizing participant burden and facilitating efficient data collection.

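### The primary model treats pre-randomisation BDI-II as an outcome visit and does not use the arms' common baseline mean: a valid test, but less efficient than it could be

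*Protocol article*

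**What the plan says.** Data Analyses in the Protocol article sets out the primary model: "The multilevel model will include time as a within-subject factor and condition as a between-subject factor". The quantity tested follows: "The interaction effect between time and condition is of main interest, as it will indicate whether the rate of change in depressive symptoms differs".

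Primary Outcome gives the visits: "The BDI-II will be measured before randomization (baseline), one week after the last session (post-intervention) and 4 weeks and 8 weeks after the last session". Sample Size describes the matching power model as "including four repeated measurement points and a random intercept for each participant". Four points can be counted only if baseline is one of them. Randomization places allocation after the introductory session, so the first BDI-II precedes it.

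Baseline BDI-II is nowhere named as a covariate, and no common baseline mean is imposed. The one covariate rule, in Data Analyses, is triggered by substantial differences between arms in demographics or the listed potential confounders. The list in Additional Measures (childhood trauma, timing of sessions, comorbidity, techniques and number of sessions in routine therapy) does not include baseline BDI-II.

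**The concern.** Because BDI-II is first measured before allocation, the two arms have the same expected baseline mean by design. A model with a free condition effect at baseline estimates two baseline means and discards that knowledge. The interaction at a visit then subtracts the whole observed baseline difference, where the data would justify subtracting only a fraction ρ of it.

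Two things are at stake. The first is precision, in a trial of 33 per arm that the Discussion itself describes as underpowered for small or medium effects. The second is the behaviour of the estimate when the arms happen to differ at baseline. That is a real possibility at this size, with enrolment allowed at any point in CBT and some patients possibly no longer meeting MDD criteria at inclusion. The covariate rule does not help: with complete data and a random intercept, a between-person covariate entered as a main effect leaves the within-person interaction unchanged.

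**Working it through.** **Inputs from the article.** N = 66, allocated equally, so n = 33 per arm; four BDI-II points including baseline; random intercept; β = 0.25 for group × time at FU2; stated power 85–90% for N of 60–70.

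**Inputs not given, therefore assumed.** Correlation ρ between baseline and follow-up (0.3 to 0.8); two-sided α = 0.05; total SD of 1 at every visit; normal approximation.

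**1. The stated power.** The scale of β is not given, so two readings were tried at ρ = 0.5.
- β = 0.25 SD per visit, linear time coded 0–3. The slope difference has variance 2(1−ρ)/(5n), where 5 is the sum of squares of 0–3 about their mean. For n = 33: SE = √(1/165) = 0.0778, 0.25/0.0778 = 3.21, power 89.5%. For N = 60 and 70, power is 86.5% and 91.1%. This agrees closely with the stated range.
- β = 0.25 SD in total at FU2, categorical time. SE = √(2·1.0/33) = 0.246, 0.25/0.246 = 1.02, power 17%. On this reading the stated range needs ρ of about 0.95.

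The stated figure can therefore be reached, but only with inputs that the article does not print.

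**2. What the interaction estimates.** With categorical time, a free condition effect and complete data, the FU2 interaction is the arm difference in mean change from baseline. In 150 simulated trials of N = 66 at ρ = 0.5, the mixed-model estimate and the change-score difference agreed to 4×10⁻¹⁵.

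**3. Variance at FU2, per arm, in units of σ²/n.**
- Free baseline: 2(1−ρ).
- Common baseline mean, or adjustment for baseline: 1−ρ².
- Ratio: (1−ρ²)/[2(1−ρ)] = (1+ρ)/2, so the share saved is (1−ρ)/2.

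| ρ (assumed) | Free | Constrained | Variance saved | SE saved | Variance saved, linear slope | Power for assumed 0.5 SD at FU2 |
|---|---|---|---|---|---|---|
| 0.3 | 1.40 | 0.91 | 35% | 19% | 40% | 40.4% → 56.7% |
| 0.5 | 1.00 | 0.75 | 25% | 13% | 26.5% | 52.8% → 65.0% |
| 0.7 | 0.60 | 0.51 | 15% | 8% | 15% | 74.6% → 81.2% |
| 0.8 | 0.40 | 0.36 | 10% | 5% | 10% | 89.5% → 92.3% |

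The simulation at ρ = 0.5 gave a variance ratio of 0.77, against 0.75 in theory.

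**4. One row in full (ρ = 0.5).** Free: SE = √(2·1.0/33) = 0.246; 0.5/0.246 − 1.96 = 0.07; power 53%. Constrained: SE = √(2·0.75/33) = 0.213; 0.5/0.213 − 1.96 = 0.39; power 65%. In sample-size terms 66/0.75 = 88: the constrained analysis of 66 patients matches the free analysis of 88.

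**5. Shift after a chance imbalance.** Given an observed baseline difference D, the expected change-score difference is the true effect minus (1−ρ)D. The SE of D is √(2/33) = 0.246 SD. A one-SE imbalance therefore shifts the estimate by 0.7 × 0.246 = 0.17 SD at ρ = 0.3, 0.12 SD at 0.5, 0.07 SD at 0.7 and 0.05 SD at 0.8.

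**The case against.** The planned model is conventional and matches the hypothesis, which concerns reductions from the pre-intervention score. The article prints no formula, so the free baseline effect is a reading of its wording. It is the natural reading, but a full analysis plan that is not shown may parameterise baseline differently. The article also mixes categorical and linear language, calling time a factor while speaking of a rate of change. Under linear time, or with missing data, the exact identity with a change score fails. All of this stands as a condition on the point. It does not remove the point: the article does state a model, its predictors and a covariate rule, none of which uses baseline BDI-II, and the linear reading loses a similar amount.

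A reader might infer that the planned test is biased or that its type I error is wrong. The documents do not support that. Allocation is random, so the change-score contrast is unbiased over repeated randomisations and the test is valid. The shift in step 5 exists only conditional on the imbalance that happens to occur.

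The 0.5 SD effect is an illustration and is not the article's figure. On the two readings of β, at ρ = 0.5, power goes from 17% to 22% (0.25 SD at FU2) or from 89.5% to 96.3% (0.25 SD per visit). On the second reading power is already adequate and the gain is modest.

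**Conclusion.** The point holds as an efficiency weakness with an inexpensive remedy. As described, and assuming a free condition effect at baseline, the primary analysis forgoes a variance reduction of (1−ρ)/2 at FU2: 35% to 10% over ρ = 0.3 to 0.8, or about 19% to 5% of the standard error. These figures rest on equal variances across visits, a random-intercept correlation and complete data.

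Two stronger statements are tempting and not supported. One is that the trial loses a quarter of its precision: that is a variance loss and needs ρ of about 0.5, which the documents do not give. The other is that the stated power is already overstated: that depends on the unstated scale of β, and one plausible reading gives about the stated range. Nor has this been compared with other possible improvements, so it cannot be ranked against them.

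**What to change.** Before any unblinded analysis, write the primary model as follows: BDI-II at all four visits, visit as a categorical factor, one baseline mean common to both arms (no condition effect at baseline), and condition × visit terms at post, FU1 and FU2.

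An alternative is to model post, FU1 and FU2 as outcomes with baseline BDI-II × visit as covariate. The two are closely similar but not identical. With a random intercept the constrained model takes its baseline weight from the single fitted within-person correlation, whereas the covariate version estimates a slope per visit. They also treat incomplete data differently.

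Apply the same choice to the secondary scales that have a baseline. If a fuller analysis plan already does this, stating it is enough. The cost is a line of model specification and a sentence of text, with no added data or patient burden.

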Current research points to the problem that the effect of ImRs on depression has not been tested sufficiently in studies yet, especially not as an adjunct to regular cognitive behavioural therapy. Furthermore, the mechanisms of action of ImRs for depression remain unclear. This randomized controlled trial aims to expand the research on ImRs in depression. The primary objective is to evaluate the effectiveness of ImRs as an add-on to standard CBT for major depressive disorder (MDD). Patients receiving CBT in routine care are randomized to receive either three sessions of ImRs or an active control condition (imagery relaxation). We hypothesize that participants in the ImRs condition will show greater reductions in depressive symptoms from pre-intervention to post-intervention and follow-up. Although ImRs may be applicable across a range of disorders (Kip et al., 2023), we chose to focus specifically on depression in the present study for several reasons: First, the high prevalence of distressing memories among individuals with depression suggests a particularly strong clinical relevance of ImRs in this context (Brewin et al., 1996; Newby & Moulds, 2011a; Payne et al., 2019). Second, existing studies have primarily evaluated ImRs as a standalone intervention; its potential additive effect when embedded within standard CBT for depression remains largely unexplored. Third, depression continues to be among the most prevalent and burdensome mental health conditions, underlining the need for innovative adjunctive treatments. Given these considerations, we see depression as a particularly meaningful starting point for examining the clinical utility of ImRs. Importantly, comorbidities are not excluded in our study, reflecting the complex presentations often encountered in routine clinical practice. Secondary objectives of this trial include examining changes in associated psychological variables (e.g., repetitive negative thinking, emotional capabilities, self-compassion, self-esteem). In addition, exploratory analyses will investigate potential mechanisms underlying the effects of ImRs.

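### The primary contrast is not fixed consistently, so the stated 85–90% power cannot be tied to the planned test and the error rate is open to a later choice of contrast

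*Protocol article*

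**What the plan says.** Four places in the protocol article bear on what the primary test is.

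- **Sample Size** states the effect behind the simulation: "Assuming a moderate group × time interaction effect (β = 0.25) at the final follow-up (FU2"). The model is a linear mixed model "including four repeated measurement points and a random intercept for each participant". Power is given as 85–90% for about 60–70 participants, and 66 are planned with equal allocation.
- **Data Analyses** describes the model: "The multilevel model will include time as a within-subject factor and condition as a between-subject factor". The interaction is the effect of main interest because "it will indicate whether the rate of change in depressive symptoms differs between the intervention and control group".
- **The objectives paragraph just before Method** states the hypothesis that the rescripting arm "will show greater reductions in depressive symptoms from pre-intervention to post-intervention and follow-up".
- **Primary Outcome** lists, after the baseline assessment, BDI-II assessments "one week after the last session (post-intervention) and 4 weeks and 8 weeks after the last session (follow-up"). None of the three is marked as the primary one.

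No alpha or sidedness is given. Correction for multiple testing is described for the secondary outcomes only.

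**The concern.** With four occasions, a group × time interaction is not one quantity. If time is categorical, there are three interaction coefficients, or one joint test on 3 degrees of freedom. If time is continuous, there is one slope difference. A contrast at the final follow-up is one of the three coefficients. These tests ask different questions and can disagree.

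The sample-size wording points to the last visit, the analysis wording to a slope, and the hypothesis to more than one visit. Two things are at stake. A reader cannot tell which test the 85–90% describes. And if the contrast is settled only once results are known, the nominal error rate no longer applies to it.

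**Working it through.** **Inputs from the protocol.** Four BDI-II occasions; random intercept; β = 0.25; 66 participants, so n = 33 per arm; stated power 85–90%.

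**Inputs assumed because none is stated.** β in units of the total SD (SD = 1); intraclass correlation ρ = 0.5, with a range of 0.3 to 0.8; two-sided 5% level; complete data; normal approximation.

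**Can the stated power be reproduced?** Not uniquely. Without the scale of β, the SD, the correlation and alpha, it can be neither confirmed nor refuted. What can be done is to see what each reading gives.

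*Reading A: difference in change from baseline at the final follow-up, 0.25 SD.*
- SE = √(4(1 − ρ)/n) = √(4 × 0.5/33) = 0.246.
- Ratio = 0.25/0.246 = 1.02, so power is about 17% (14% at ρ = 0.3, 36% at ρ = 0.8).
- One-sided testing at 5% raises it only to about 26%.
- Reaching 85–90% would need ρ of 0.943 to 0.951.

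*Reading B: linear slope difference of 0.25 SD per occasion, time coded 0, 1, 2, 3 (sum of squares 5).*
- SE = √(2(1 − ρ)/(5n)) = √(1/165) = 0.0778.
- Ratio = 0.25/0.0778 = 3.21, so power is about 89% (77% at ρ = 0.3, above 99% at ρ = 0.8).
- 85–90% corresponds to ρ of 0.43 to 0.51.
- The implied difference at the final follow-up is 3 × 0.25 = 0.75 SD.

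*Reading C: linear slope that totals 0.25 SD by the final follow-up.*
- Slope = 0.25/3 = 0.0833; ratio = 0.0833/0.0778 = 1.07; power is about 19%.

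*Reading D: joint 3-df interaction test, 0.25 SD at the final follow-up only.*
- Noncentrality = 33 × 0.25² × 3/4 = 1.55 at ρ = 0.5; power is about 16%.

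At the same N and the same nominal β, power runs from about 16% to about 89% depending on the definition.

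**Type I error.** I simulated two million null data sets with equal correlation between occasions and a two-sided 5% level for each test.

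| What may be declared positive | Error |
|---|---|
| Any one test fixed in advance (final follow-up, slope or joint) | about 5% |
| Final follow-up or slope | about 6% |
| Final follow-up, slope or joint test | about 9% |
| Final follow-up, slope or post-intervention | about 10% |
| Any of the three post-baseline contrasts | about 12.5% |

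**Does the choice between slope and final-visit contrast matter for a given true effect?** Take weeks 0, 4, 7 and 11 from the visit schedule (mean 5.5, sum of squares 65) and ρ = 0.5. The slope SE is √(1/(65 × 33)) = 0.0216.
- Benefit of 0.5 SD present from post-intervention and held: slope = 5.5 × 0.5/65 = 0.0423, power about 50%; final-visit contrast = 0.5/0.246 = 2.03 SE, power about 53%.
- Benefit growing linearly to 0.5 SD: slope = 0.5/11 = 0.0455, power about 56%; final-visit contrast about 53%.

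Neither test is clearly better. The problem is that the text does not settle on one.

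**The case against.** The strongest reply is that both sections name the same thing, a group × time interaction in a mixed model of the same outcome. A coefficient at the final follow-up is part of that interaction when time is categorical. Calling time a within-subject factor is common design language and does not prove categorical coding; rate of change is often used loosely; and the hypothesis is plain-language introduction, not a test definition. A condensed article may also leave time coding, contrast and alpha to a fuller plan or to the registration, neither of which is shown.

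Much of this stands, and it rules out two stronger readings that a reader might infer.

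- *That the powered test is shown to differ from the planned one.* It is not. Reading B reproduces 85–90% at ordinary correlations, so the simulation may have used the slope test. All that can be said is that the match cannot be confirmed.
- *That a 5% error rate is not held.* This does not follow. There is one primary outcome and one effect of main interest; no passage lets significance at any visit count as success; and no alpha is stated. Correcting only the secondary outcomes is consistent with a single primary test. The 12.5% belongs to a decision rule that the article does not adopt.

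Nor is a slope analysis wrong in itself, as the last comparison in the working shows.

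What does not stand is the appeal to an unseen plan. The point is not that detail is absent. The article commits to the final follow-up in one section and to a rate of change in another, and a relied-on power figure hangs on which is meant.

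**Conclusion.** The inconsistency is real and worth correcting. The stated power cannot be linked to the planned test, and the link matters: about 17% as a contrast of 0.25 SD at the final follow-up against about 89% as a slope of 0.25 SD per occasion. The latter presupposes 0.75 SD at that visit, which sits uneasily with an effect described as moderate. These figures rest on the assumed SD scale, ρ = 0.5, two-sided 5% and no dropout.

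Type I error is about 5% for any single test fixed in advance. The text leaves it unprotected, rather than inflated: about 6% to 12.5% would apply only if the choice among readings came later or any of several could count.

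**What to change.** 1. Name one primary test with a single degree of freedom, before outcomes are analysed by condition. The simplest choice is the condition difference in BDI-II change from baseline to the final follow-up, with time categorical, because the sample-size section already points there. A pre-specified slope would be equally valid if that section is rewritten to match.
2. State alpha and sidedness.
3. Restate power for that test, giving the scale of β, the SD and the intraclass correlation.
4. Label the remaining visit contrasts, the joint interaction test and whichever of slope or final-visit contrast is not chosen as secondary.
5. Align the wording of the hypothesis, Sample Size and Data Analyses; if the final-visit contrast is chosen, remove the rate-of-change phrase from the primary definition.

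The cost is wording, a rerun of the power calculation and, if the primary time point is not already fixed in the registration, an update there. No visit, measure or recruitment target has to change to make the text consistent, although the restated power may turn out lower than the one now given.
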